#### Control Group:

Consecutive patients with cancer who have clinical indication to start checkpoint inhibitors will be approached for consent to be enrolled in the study. We will enrol 120 consecutive patients who will be identified as controls. A small proportion of patients will develop ChILI following their checkpoint inhibitor treatment and will be classified as cases.

### **Exclusion criteria**

Anyone with any of the following conditions will not be included in the study:

- Patients who are treated with cytotoxic chemotherapy concurrently with checkpoint inhibitors.
- On the judgement of CI that the person has certain alternative explanation to the acute event (rather than ChILI).

### **Informed consent**

We will obtain informed consent from participants or their consultee in case they lack capacity to consent. The Informed Consent Form will be signed and dated before they enter the trial. The Investigator will explain the details of the trial and provide a Participant Information Sheet/Consultee Information Sheet, ensuring that the participant/consultee has sufficient time to consider participating or not and ask questions about the study.

The process for obtaining participant informed consent will be in accordance with the REC guidance, and Good Clinical Practice (GCP) and any other regulatory requirements that might be introduced. Since patients who develop acute checkpoint inhibitors liver injury can often present in emergency departments with sudden onset of severe symptoms, a long period (e.g. 24h) to consider consent is often difficult to provide in order to recruit patients while symptomatic and without asking patients to make additional hospital visits. Therefore, where appropriate patients will be given a reasonable time period (at least 1 hour without disturbance), to read the patient information sheet and consider enrolment before being approached for consent by the research team. Appropriate steps will be taken

to ensure that the patient is able to discuss participation in the study with those not involved in the research. The investigator or their nominee and the participant or other legally authorised representative shall both sign and date the Consent Form before the person can participate in the study.

The participant will receive a copy of the signed and dated forms and the original will be retained in the study records. A second copy will be filed in the participant's medical notes and a signed and dated entry made in the notes that informed consent was obtained for the study. Due to COVID-19 pandemic, we will also consider electronic consent (e-consent) through the secure website (REDCap) as a method of obtaining informed consent to reduce face to face contacts with patients.

The decision regarding participation in the study is entirely voluntary. The investigator or their nominee shall emphasize to them that consent regarding study participation may be withdrawn at any time without penalty or affecting the quality or quantity of their future medical care, or loss of benefits to which the participant is otherwise entitled. No study-specific interventions will be done before informed consent has been obtained.

The investigator will inform the participant of any relevant information that becomes available during the course of the study, and will discuss with them, whether they wish to continue with the study. If applicable they will be asked to sign revised consent forms.

If the Consent Form is amended during the study, the investigator shall follow all applicable regulatory requirements pertaining to approval of the amended Consent Form by the REC and use of the amended form (including for on-going participants).

### **Participants who lack capacity to consent to research**

Due to the nature of the study some potential participants may lack capacity to give informed consent. This is especially likely in the case of hepatic encephalopathy, which is the occurrence of confusion, altered level of consciousness, and coma as a result of liver failure. It is important that we try to enrol such patients where possible into this study, as research into this area may be of benefit to future patients with this condition. As the study has minimal risk to the patient, we believe that the benefits of enrolling such patients outweigh the potential risk.

We have referred to the mental capacity act in our decision to enrol patients who lack capacity. There are a number of provisions specific to research that we have taken into account. It is noted that the research in question will be connected with the impairing condition affecting the participant. We will only seek consent from those who lack capacity in a way that is related to their liver injury. We therefore will not seek consent from those who would have been likely to lack capacity before any liver injury has occurred. We will therefore not be enrolling patients who are believed to have a "double impairment". Secondly, we believe that research of equal effectiveness cannot be carried out if confined to participants with capacity, as, the most severe cases of the condition we are researching, can cause impairments. We believe that it is important to include the most severe cases in our research. Thirdly, although our research does not directly benefit the patient, this research will provide knowledge of the causes or treatment of others with the same condition, and involves negligible risk to the participant, does not interfere significantly with freedom of action or privacy, and is not unduly invasive or restrictive.

If the PI or Investigator has reason to suspect that a person may lack capacity, that individual will be assessed according to normal local hospital procedures. If the person is found to lack capacity then the research team will ask someone close to that person if they would consider acting as their personal consultee, e.g. next of kin, a relative, spouse, close friend. The personal consultee should be someone the person who lacks capacity would trust with important decisions about their welfare.

If the PI or Investigator and research team are unable to identify/appoint a suitable personal consultee then efforts will be made to nominate a health professional who is unconnected with the research project to act as a professional consultee. We will firstly ask a member of the standard medical care team of the person who lacks capacity if they would consider taking on the role. The professional consultee will be required to perform the same role as a personal consultee in advising the research team but they may not know the person who lacks capacity and therefore may be required when attempting to determine what the person's wishes and feelings about the research would be if they had capacity, seek the views of any family, friends/carers of the person who lacks consent, or seek other professional colleagues with an interest in the person's welfare or condition. We will continue to assess capacity throughout the research and will seek consent as soon as feasible.

All consultees (personal and professional) will receive a copy of the consultee information sheet to read. If and when the participant regains capacity, consent will be sought from the participant retrospectively, and will be withdrawn from the study if consent is not given.

We currently have no sites or plans to recruit from sites in Northern Ireland. If this was to occur, we are aware that Northern Ireland follow different legislation and a different process would need to be followed regarding the documentation. We would ensure that this process was followed correctly. We are currently seeking approval to recruit these patients in England and Wales only. We plan to put a future application to a Scotland A REC in order to allow us to recruit patients who lack capacity in Scotland.

## STUDY TREATMENT AND REGIMEN

Suspected ChILI patients:

Biological samples will be collected from each enrolled patient on three occasions. These visits will take place as soon as possible following acute presentation; there will be a time lag of up to 2 weeks between identification of an episode of ChILI by the team responsible for the clinical care of the patients and the patient giving consent to take part in the study. Patients' blood tests must meet the eligibility criteria on the day they are enrolled (Day 0, visit 1) in order to participate in the ChILI study. Visit 2 will be 2-14 days from Visit 1. Visit 3 will be  $30 \pm 7$  days after the Visit 1.

As far as possible, research bloods will be collected at the same time as bloods for clinical care of the patient and visits arranged to coincide with hospital appointments. Preferred visit times are given below but visits outside the times will not be considered as a protocol deviation.

Appendix 1 lists the standard clinical care analyses (including ultrasound, viral hepatitis screen, autoantibody screen, haematology and blood chemistry), and research assessments which will be carried out at each visit.

For those who are in-patients (hospitalised at the time of acute ChILI) samples will be collected as part of clinical care and additional samples collected for research purposes.

At each visit a delegated member of the research team will collect:

- Up to 80ml of blood. See most recent study presentation and/or sample collection SOP for details.
- Up to **20 ml of urine if possible**
- A Stool sample will also be collected (if possible).

When considered appropriate by the clinical team, an additional optional 30ml blood will be requested at one or two visits. This will be collected in EDTA anti-coagulated tubes and

transferred directly to the research lab for processing immediately where this facility is available.

Patients may be consented and samples collected at their home if appropriate and with permission of the PI. Nursing staff would be required to follow their Trust's lone working policy and code of practice.

All biological samples will be processed according to the standard operating procedures labelled and stored at -80°C in Nottingham Digestive Diseases Centre. If a liver biopsy is obtained for clinical reasons, any samples available (when the liver biopsy core is >25 mm) will be collected and stored for research purposes. Fresh liver tissue will be snap frozen in liquid nitrogen or placed in RNA later prior to storage at -80°C. (We will also aim to obtain and store any archived liver sections that were taken as part of clinical care). The liver biopsy specimens will be reviewed centrally by [name].

#### Control group

Prior starting checkpoint inhibitor treatment, patients will have a baseline visit when biological samples will be collected (blood, stool and urine sample) and processed as described for ChILI patients visit 1. Further visit will take place 6-14 weeks after starting CPI treatment. Demographic data and medical and pharmacological history will also be collected as outlined in the CRF

#### Sample size and justification

This is a mechanistic study to document the disease natural history rather than evaluate performance of specific biomarkers. As this uses specialist methods, we will only be able to recruit from a small number of suitable sites near to analytical facilities so sample size is limited by availability of suitable participants. Due to rarity of checkpoint inhibitors induced liver injury, incidence rate are between 3-18 % of patients receiving CPI, we aim to enrol 40 cases and 120 controls who received CPI without developing liver injury over 3 years. This is feasible at this centre based on current records of CPI treatment.

## **ADVERSE EVENTS**

### **Definitions**

**An adverse event is any unfavourable and unintended sign, symptom, syndrome or illness that develops or worsens during the period of observation in the study.**

An AE does include a / an:

1. Exacerbation of a pre-existing illness.
2. Increase in frequency or intensity of a pre-existing episodic event or condition.
3. Continuous persistent disease or symptoms present at baseline that worsen following the start of the study.

A Serious Adverse Event (SAE) is any untoward and unexpected medical occurrence or effect that:

- Results in death
- Is life-threatening – refers to an event in which the subject was at risk of death at the time of the event; it does not refer to an event which hypothetically might have caused death if it were more severe
- Requires hospitalisation, or prolongation of existing inpatients' hospitalisation

Page 18 of 29

ChILI Protocol Final V1.6 / date 26/02/2024

|                                                                                                                                                                                                                                         |
|-----------------------------------------------------------------------------------------------------------------------------------------------------------------------------------------------------------------------------------------|
| This protocol is confidential and the property of the University of Nottingham. No part of it may be transmitted, reproduced, published, or used by other persons without prior written authorisation from the University of Nottingham |
|-----------------------------------------------------------------------------------------------------------------------------------------------------------------------------------------------------------------------------------------|

- Results in persistent or significant disability or incapacity
- Is a congenital anomaly or birth defect

Important medical events that may not result in death, be life-threatening, or require hospitalisation may be considered a serious adverse event when, based upon appropriate medical judgment, they may jeopardize the patient or participant and may require medical or surgical intervention to prevent one of the outcomes listed in this definition

AE doesn't include a/ an:

1. Exacerbation of a pre-existing illness or progression of underlying malignancy.
2. Increase in frequency or intensity of a pre-existing episodic event or condition.
3. Condition detected or diagnosed after medicinal product administration even though it may have been present prior to the start of the study.
4. Continuous persistent disease or symptoms present at baseline that worsen following the start of the study.
5. Medical or surgical procedure (e.g., surgery, endoscopy, tooth extraction, transfusion); but the condition that lead to the procedure is an AE.
6. Pre-existing disease or conditions present or detected at the start of the study that did not worsen.
7. Situations where an untoward medical occurrence has not occurred (e.g., hospitalisations for cosmetic elective surgery, social and / or convenience admissions).
8. Disease or disorder being studied or sign or symptom associated with the disease or disorder unless more severe than expected for the participant's condition.
9. Overdose of concurrent medication without any signs or symptoms.

All adverse events will be assessed for seriousness and expectedness:

A distinction is drawn between serious and severe AEs. Severity is a measure of intensity whereas seriousness is defined using the criteria above. Hence, a severe AE need not necessarily be serious.

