### **NHS secondary care hospital sites in the UK (Including Scotland)**

#### **Primary endpoint**

Following acquisition of clinical samples and collation of associated comprehensive demographic, phenotypic and clinical data collected from a total of: 40 patients who develop checkpoint inhibitors-induced liver injury (ChILI) and 120 patients with cancer are treated with checkpoint inhibitors, we aim to:

1. Measure the incidence of liver injury secondary to checkpoint inhibitors and other adverse events.
2. Identify and characterise biomarkers associated with ChILI.

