### Serious AEs

An SAE form should be completed and faxed to the Chief Investigator within 24 hours. A Serious Adverse Event (SAE) is any adverse event occurring following study mandated procedures, having received the treatment or intervention that results in any of the following outcomes. However, acute liver failure, liver transplantation and death are recognised consequences of DILI and these will be recorded as part of the outcome of DILI as recommended by consensus criteria [40]. Therefore, following will NOT be considered as SAE:

1. Liver related death
2. Acute liver failure
3. Liver transplantation
4. Inpatient hospitalisation or prolongation of existing hospitalisation
5. A disability / incapacity

In the current study we will be performing venepunctures for blood sampling. So, we will report major bleeding leading to hypotension, drop in Hb, requirement of resuscitation, transfusion or hospital admission as adverse events. All SAEs should be reported to the North West - Haydock Research Ethics Committee where in the opinion of the Chief Investigator, the event was:

- 'related', ie resulted from the administration of any of the research procedures; and
- 'unexpected', ie an event that is not listed in the protocol as an expected occurrence

Reports of related and unexpected SAEs should be submitted within 15 days of the Chief Investigator becoming aware of the event, using the COREC SAE form for non-IMP studies.

Local investigators should report any SAEs as required by their Local Research Ethics Committee and/or Research & Development Office.

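### Three kinds of event are defined both as adverse events and as not adverse events, and hospitalisation and disability both are and are not criteria for a serious adverse event

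*Protocol*

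**What the plan says.** Under ADVERSE EVENTS, the Definitions section of the protocol first defines an AE in general terms as something unfavourable that "develops or worsens during the period of observation in the study". It then names three things that an AE includes: "Exacerbation of a pre-existing illness"; "Increase in frequency or intensity of a pre-existing episodic event or condition"; and "Continuous persistent disease or symptoms present at baseline that worsen following the start of the study".

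Later in the same section a nine-item list sets out what an AE does not include. Item 1 is "Exacerbation of a pre-existing illness or progression of underlying malignancy". Items 2 and 4 repeat the second and third inclusions word for word. Item 6 excludes pre-existing conditions that did not get worse.

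On seriousness, Definitions gives five bulleted criteria. One is "Requires hospitalisation, or prolongation of existing" inpatient stay; another is lasting or significant disability or incapacity. A separate paragraph allows important medical events to be judged serious.

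The Serious AEs section says that acute liver failure, transplantation and death are recognised outcomes of drug-induced liver injury and will be recorded as such. It then lists five things that will not be treated as SAEs. Item 1 is confined to liver-related death. Item 4 is "Inpatient hospitalisation or prolongation of existing hospitalisation" and item 5 is disability or incapacity; neither has a qualifier.

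Item 1 of the primary endpoint is to "Measure the incidence of liver injury secondary to checkpoint inhibitors and other adverse events".

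**The concern.** A site has to decide for each event whether it is an AE and, if so, whether it is serious. For any worsening of a condition the patient already had, the protocol gives both answers to the first question. For any admission or disability, it gives both answers to the second.

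Two things are at stake. The first is safety reporting. The 24-hour form and the ethics-committee report for related and unexpected events apply only to SAEs, so an event exempted from SAE status drops out of both. The Non-serious Adverse Event section describes blood sampling as the study's only intervention, so harm from that procedure is what the reporting route most needs to catch.

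The second is the count of other adverse events in item 1 of the primary endpoint. Proposal Aims, Statistical analysis and Primary Outcome Measure narrow it to immune-related or immune-mediated events. The protocol gives no separate definition of such an event. In a multi-centre study, one site could count the worsening of a pre-existing immune condition on treatment while another leaves it out.

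**Working it through.** No figure in the protocol is in question and no formula applies. The check sets the lists side by side.

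**AE lists (both in Definitions)**

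| Event | Counts as an AE | Does not count as an AE | Match |
|---|---|---|---|
| Exacerbation of a pre-existing illness | Item 1 | Item 1 | Same, with progression of malignancy added to the exclusion |
| Increase in frequency or intensity of a pre-existing condition | Item 2 | Item 2 | Identical |
| Baseline disease or symptoms that worsen | Item 3 | Item 4 | Identical |

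So 3 of the 3 inclusions also stand among the 9 exclusions. No reading satisfies both lists, because the same event is named in each. Two other statements in the section side with the inclusion list. The general definition counts worsening, and exclusion item 6 removes pre-existing conditions only if they did not worsen, which would be superfluous if worsened ones were excluded too. Exclusion items 1, 2 and 4 are therefore the outliers, apart from the reference to malignancy in item 1, which has no counterpart among the inclusions.

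**SAE criteria**

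| Criterion in Definitions | Treatment in Serious AEs |
|---|---|
| Death | Exempt only if liver-related |
| Life-threatening | Not exempted as such |
| Hospitalisation or its prolongation | Exempt, no qualifier |
| Disability or incapacity | Exempt, no qualifier |
| Congenital anomaly | Not exempted |
| Important medical event (separate paragraph) | Not exempted |

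Of the 5 bulleted criteria, 2 are negated outright and 1 in part. The qualifier on death shows that the list restricts an item when it means to.

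**Following an event through the text.** Take an admission caused by a research blood draw that is not life-threatening and is not judged an important medical event.

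1. Under Definitions it is serious, because it required hospitalisation.
2. Under item 4 of the exemptions in Serious AEs it is not an SAE.
3. If it is not an SAE, neither the 24-hour form nor the ethics-committee report applies.
4. Serious AEs does name major bleeding after venepuncture, including bleeding that leads to hospital admission, but as something to report as an adverse event. It does not say that such bleeding is an SAE, so step 2 stands.

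**Effect on the primary endpoint.** The effect on the incidence of other events equals the share of those events that are worsenings of pre-existing conditions. The protocol gives no such share, so the size cannot be computed. ChILI is defined by laboratory thresholds for ALT, bilirubin and ALP, together with exclusion of other causes. Neither its incidence nor the case-control biomarker comparison depends on the AE lists.

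**The case against.** The best defence of the SAE exemptions is their context. The list follows directly from a sentence on recognised outcomes of drug-induced liver injury, so it can be read as a carve-out for the disease under study, whose outcomes are recorded anyway. That is probably the intention. But the text does not say so for admission or disability, while it does for death, and sites can apply only what is written.

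It is also fair to say that the AE lists sit in a safety section, and that nothing states that immune-related events will be counted by them. The endpoint consequence is therefore a possibility, not a demonstrated error.

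Three stronger readings are tempting, and the protocol does not support them.

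- A reader might infer that a serious bleed from a research blood draw can never reach the ethics committee. Major bleeding is named for reporting, and an event that is life-threatening or an important medical event can still qualify as an SAE. The gap is confined to events whose only claim to seriousness is admission or disability.
- A reader might infer that half of the primary endpoint fails. Item 1 combines ChILI incidence with other adverse events, and item 2 concerns biomarkers. Only the part on other events is exposed.
- A reader might infer from Appendix 1, which has no row for immune-related events, that these are not collected. The description of the cohort study provides for medical and clinical data at both visits, the Non-serious Adverse Event section requires such events to be recorded, and the electronic case report form is not shown.

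**Conclusion.** The point holds for the wording of the safety section. The AE definition contradicts itself on all three of its inclusions, and the protocol both makes and cancels two of its five bulleted SAE criteria. These are conflicts within the current text.

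The firm consequence is for safety reporting. On a literal reading, a procedure-caused admission or disability that meets no other seriousness criterion is outside the 24-hour and ethics-committee routes. This rests on taking exemption items 4 and 5 as written, without an implied limit to liver injury.

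The consequence for the primary endpoint is limited: possible inconsistency between sites in counting worsened pre-existing immune conditions, of a size that the protocol does not allow one to compute. It rests on the assumption that sites use the AE lists when they decide what to count. ChILI incidence and the biomarker comparison stand. The correction is cheap and the conflicting rules govern reporting at every site, so it should be made.

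**What to change.** 1. Reconcile the two AE lists so that each kind of event appears in only one. Removing the duplicated items 1, 2 and 4 from the exclusion list, while keeping progression of the underlying malignancy as an exclusion, would agree with the general definition and with exclusion item 6.
2. Reconcile the SAE criteria in Definitions with the exemptions in Serious AEs by stating the scope of exemption items 4 and 5. The wording should leave events caused by study procedures reportable as SAEs, in keeping with the section's own rule for related and unexpected events. The sentence on venepuncture bleeding should say whether bleeding that leads to admission is an SAE.

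The cost is amendment wording and a few more recorded events. No change to sample size, visits or the planned analyses is needed.
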